#### Aim 2 (Symptom Network Differences Across Behavioral Profiles).

Person-centered analytic approaches will be used to identify distinct 24-hour movement behavior composition profiles. Depending on distributional properties and model fit, approaches may include latent profile analysis, model-based clustering, or related mixture modeling techniques. Model selection will be guided by statistical fit indices (e.g., Bayesian Information Criterion), classification quality, theoretical interpretability, and class size considerations. Following profile identification, separate mlVAR models will be estimated within each behavioral subgroup to construct profile-specific symptom-behavior networks. Network comparison tests will be used to evaluate differences in global network strength, edge weights, and overall network structure between profiles.

#### Aim 3 (Periods of Heightened Risk for Symptom Onset and Progression).

To examine the temporal stability of the depression symptom network across the first college term, including 24-hour movement behaviors and anxiety symptoms as nodes, time-varying network analyses will be conducted using rolling 7-day calendar windows across the 108-day study period.^103^ Although participants contributed data during assigned burst weeks only, pooled daily observations across individuals provide coverage spanning the full academic term. Within each window, mlVAR models will be estimated to derive temporal (lagged) and contemporaneous networks while accommodating the unbalanced repeated-measures structure of the burst design. Window-specific network metrics, including global connectivity (e.g., average edge weight), network density, and node centrality indices, will be computed to evaluate changes in overall interconnectedness and node influence over time. Periods characterized by increased network connectivity or heightened centrality of specific symptoms or behaviors will be interpreted as potential windows of increased vulnerability – or, conversely, relative stability – during the transition to college. Calendar-based academic or institutional events (e.g., midterm periods, finals week, university-designated mental health initiatives such as Wildcat Pause Day) will be descriptively overlaid onto temporal network estimates to contextualize observed patterns.

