The purpose of this paper is to describe the protocol and baseline characteristics of the College Adjustment, Lifestyle and Mental Health (CALM) Study, an intensive longitudinal cohort study designed to examine dynamic relationships between device-assessed 24-hour movement behaviors and depressive symptoms during the transition to college. Specifically, this study aims to characterize day-to-day associations between 24-hour movement behaviors and individual depressive symptoms, describe movement behavior patterns associated with elevated risk for depressive symptom onset and progression, and identify periods of heightened vulnerability during the transition to college.

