## Methods

### Study Design

The CALM Study was a prospective cohort study that followed first-year undergraduate students for 108 days (September 2-December 19, 2025) during their transition into their first academic term at university. Participants were onboarded between August 25 and September 5, 2025. The study employed a hybrid panel-burst design to capture both longer-term changes across the semester and short-term, day-to-day fluctuations in depressive symptoms and 24-hour movement behaviors. This design is consistent with recommendations for measurement-burst designs that integrate intensive short-term assessment within longer-term longitudinal follow-up to distinguish within-person dynamics from broader developmental change.^45,46^

Participants (N = 144) completed five panel surveys administered at four-week intervals following baseline to assess broader psychosocial and contextual factors across the semester. In parallel, five 7-day intensive daily assessment bursts were distributed across the study period (Days 1–21, 22–42, 43–62, 63–82, and 90–108). The intensive burst design was selected as it optimally balances long study windows with reduced participant burden in smartphone-based research.^47^ Burst timing was randomized within predefined calendar windows and did not align systematically with panel survey administration. No bursts were scheduled during Fall break (Days 83–89) to avoid confounding assessments with atypical routines and travel-related disruptions.

To minimize systematic timing effects across the academic term while preserving calendar balance, burst timing was randomized using a constrained block allocation schedule. The 108-day study was divided into five consecutive calendar periods (four 20–21 day windows during the semester and a final 19-day window following fall break). Each period contained three potential 7-day burst windows corresponding to Early, Mid, and Late segments of the period (Fig. 1). Participants were assigned to one of six pre-specified burst sequences (S1-S6), each representing a unique ordering of Early, Mid, and Late burst timing across the five study periods. A fixed set of sequences was used to ensure exact balance across burst positions while maintaining feasibility within the study platform. This allocation scheme was developed to satisfy the feasibility and balance constraints outlined in Table 1.

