During each 7-day burst period, participants completed a daily diary adaptation of the PHQ-8 assessing symptoms experienced since waking that day.^63^ Item selection and wording were informed by an established experience sampling repository (i.e., the ESM Item Repository) to ensure ecological validity and alignment with intensive longitudinal measurement practices.^64^ Items are presented in Supplementary Materials Table 1. The suicidality item was excluded due to safety monitoring constraints in unsupervised daily assessment contexts. To enhance conceptual specificity for network modeling, selected items were decomposed into theoretically distinct components. Specifically, the psychomotor agitation/retardation item was separated into two items distinguishing slowed movement/speech from restlessness, and the sleep item was divided to differentiate difficulty initiating or maintaining sleep (“trouble falling asleep or staying asleep”) from hypersomnia-related symptoms (“slept more than usual”). As a result of these modifications, the daily diary instrument included 10 depressive symptom items. Daily items were rated on a five-point scale ranging from 0 (“Not at all”) to 4 (“Very much”) and were administered at 8:00 pm, with automated hourly reminders at 9:00 pm and 10:00 pm before the survey closed at 11:00 pm. To support participant well-being, information about free university psychological services was provided upon completion of each daily diary.

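### Aim 3 re-estimates a 17- to 19-node network in every rolling 7-day window, so apparent connectivity can move with the burst schedule and the fall-break gap when nothing real has changed

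*Protocol article*

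**What the plan says.** The Aim 3 section of Data Analyses fixes four things.

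- **Window:** "time-varying network analyses will be conducted using rolling 7-day calendar windows across the 108-day study period".
- **Model:** "Within each window, mlVAR models will be estimated to derive temporal (lagged) and contemporaneous networks". The depression network is the base, "including 24-hour movement behaviors and anxiety symptoms as nodes".
- **Metrics:** average edge weight, density and node centrality for each window.
- **Reading rule:** "Periods characterized by increased network connectivity or heightened centrality of specific symptoms or behaviors will be interpreted as potential windows of increased vulnerability".

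The section justifies the windows by saying that "pooled daily observations across individuals provide coverage spanning the full academic term". Study Design, however, states: "No bursts were scheduled during Fall break (Days 83–89".

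On the node set, the depressive symptoms section says "the daily diary instrument included 10 depressive symptom items". The anxiety section describes 6 daily items. The Preparation section turns a four-part composition into ilr coordinates.

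**The concern.** Each person was observed in five separate 7-day bursts. A 7-day window that moves along the calendar sometimes coincides with one burst slot and sometimes cuts across two. The number of people in a window, and above all the number of consecutive days per person, therefore changes with alignment. Network estimates from very short series are biased and noisy, and both problems depend on series length. If the metrics respond to that length, a network that never changes will appear to tighten or loosen. The plan would then label some of that movement as vulnerability, and it overlays midterms and finals on the same curve.

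**Working it through.** **Inputs from the article.** There are 144 enrolled participants and one 7-day burst per person per period. Table 1 puts two of six sequences in each Early, Mid or Late slot and excludes late-to-early transitions. The diary has 10 depressive and 6 anxiety items. A four-part composition has 3 ilr coordinates. No diaries fall on Days 83–89.

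**Assumptions.** Equal sequence sizes, full compliance unless stated, and a 1-day step (the step is not given). Exact slot dates in the 20- and 19-day periods are also assumed, because the figure is not shown.

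**Reference figure.** The article gives no sample-size figure for Aim 3. Its power statement rests on 30–35 daily observations per person, and 5 × 7 = 35 reproduces the upper end. An Aim 3 window holds at most 7.

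**Nodes and edges.** 10 + 6 + 3 = 19 nodes, or 17 if only the pivot coordinate enters. That is 19² = 361 or 17² = 289 temporal edges.

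**Lag pairs per window.** No window can catch two bursts of one person, so the maximum is 7 − 1 = 6 pairs each.

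- Aligned with a slot: 144/3 = 48 people × 6 = 288 pairs.
- Three or four days off: 48 × 3 + 48 × 2 = 240 pairs, from 96 people with 2 or 3 pairs each.

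**Short-series bias, single node.** For true autoregression φ and T pairs, the Nickell result gives an expected within-person estimate of φ − [(1+φ)A/(T−1)] / [1 − 2φA/((1−φ)(T−1))], with A = 1 − (1−φ^T)/(T(1−φ)). With φ = 0.25:

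- T = 6: A = 0.778, so 0.25 − 0.194/0.896 = +0.03
- T = 3: A = 0.5625, so 0.25 − 0.352/0.8125 = −0.18
- T = 2: A = 0.375, so 0.25 − 0.469/0.75 = −0.375

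**Simulated constant network.** The set-up was 19 nodes, autoregression 0.25, mean absolute cross-edge 0.028, and pooled person-centred least squares in each window. True mean absolute edge including self-loops is (19 × 0.25 + 342 × 0.028)/361 = 0.040.

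| Quantity, centred within the window | Aligned | 3–4 days off |
|---|---|---|
| Mean autoregression | +0.02 | −0.30 |
| Mean absolute edge, with self-loops | 0.068 | 0.083 |

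One day off alignment, the autoregression is about −0.03. Off-diagonal edges alone stay between about 0.067 and 0.077 across alignments. They hardly cycle, but are inflated by noise to 0.067/0.028 = 2.4 times truth or more.

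A second simulation (autoregression 0.30, no cross-lags) gave the same pattern: mean absolute edge 0.066 aligned and 0.090 mid-slot, autoregression +0.06 and −0.22. When 40 cross-lags of 0.08 were added, the signed average edge fell from 0.010 to −0.007 while the absolute average rose from 0.069 to 0.091. Direction therefore depends on the metric.

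**Centring on all burst days instead.** With the same rolling windows, the autoregression is flat near 0.20 at every alignment.

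**Fall break.** 108 − 7 + 1 = 102 windows. Those starting on Days 77–89, 13 in all, overlap the break. Windows starting on Days 77, 78, 79, 80 and 81 hold 240, 192, 144, 96 and 48 pairs, and those starting on Days 82–84 hold none. By the window with three diary days left (96 pairs), mean absolute edge has climbed from about 0.07 to between 0.11 and 0.13. This happens under either centring, with no true change.

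**The case against.** The strongest reply is that the article does not say where person means are computed, and a full analysis plan may settle it. With all-burst centring the cyclic swing in autoregression disappears. That stands. A reader might infer that any stable network must show a 7-day sawtooth in connectivity. The documents do not support that, because the swing lies mainly in self-loops and depends on centring within the window. The article's wording, with models estimated inside each window, leads to that centring but does not state it.

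It can also be said that the plan wants pooled window-level metrics, not person-specific networks, that Limitations concedes the reliance on pooling, and that Study Design discloses the break openly. All true. None of it removes the noise inflation or the rise into the break, which persist under either centring. Nor does it reconcile the coverage sentence with the schedule.

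Four further inferences should be resisted:

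- Break windows do not lack all data. Fitbit wear continues, and only the Days 83–89 window is wholly without diaries.
- Peaks in low-compliance weeks cannot be asserted, since the article gives no compliance figures.
- That the monthly PHQ-8 goes unused in modelling onset or progression would be an argument from silence in a condensed article.
- Collapsing symptoms into scores, or requiring a concurrent symptom rise, would cut against the stated symptom-level purpose and the Discussion's idea that connectivity may rise before symptoms do.

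**Conclusion.** The point holds in a bounded form. At most 6 pairs per person, and 240 to 288 pairs per non-break window at full compliance, follow from the schedule under the stated slot and step assumptions. Given within-window centring, a constant network yields autoregression from about +0.02 down to −0.30, and mean absolute edge weight from about 0.07 to 0.08. Under either centring, off-diagonal edges exceed twice their true size and the absolute metric rises to about 0.11–0.13 at the edge of the break. These sizes depend on the assumed autoregression, cross-edges, compliance and pooled estimator. The coverage sentence contradicts the schedule for symptom data whatever those assumptions are.

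A reader might conclude that Aim 3 cannot answer its question at all. That goes too far. The Abstract places network stability among secondary analyses, the article speaks only of potential windows, and Limitations calls lagged findings hypothesis-generating. The weight is moderate: as fixed, the reading rule has no safeguard against movement produced by the design itself.

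**What to change.** Keep the symptom-level nodes. Replace the window-by-window fits with one multilevel VAR pooled over all bursts, centred on all of a participant's burst days, with lagged edges moderated by study period (P1–P5) or by study day. Each period then has up to 144 × 6 = 864 pairs, at a constant 6 per person. Include period terms for symptom and behaviour levels, so that shifts across the semester are not absorbed into the lagged edges.

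Give intervals for change in connectivity by resampling participants. Describe a period as one of increased vulnerability only if the change exceeds that uncertainty. State whether the connectivity metric is signed or absolute and whether it includes self-loops. Report no symptom-network estimate for Days 83–89, and amend the coverage sentence to exclude those days.

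The cost is a rewording of the analysis section; no new data are needed. The real loss is time resolution: five periods or a smooth trend instead of a daily-moving window, which makes the overlay of single calendar events coarser.

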### Sample Size Calculation

The present study was powered based on the intensive burst (daily diary) component rather than the monthly panel surveys, as primary hypotheses focused on within-person daily associations between 24-hour movement behaviors and depressive symptoms. Sample size considerations for intensive longitudinal designs are influenced by the number of participants, number of repeated observations per participant, and expected within-person effect sizes.^48,49^ Daily diary studies examining PA and affect, including negative affect items that reflect depressive symptoms, have typically observed small within-person effects.^50–53^ Assuming a small effect size (d = 0.20) and approximately 30–35 daily observations per participant across the five bursts, simulation-based estimates suggested that approximately 107 participants would provide 80% power to detect within-person effects.^54,55^ Allowing for up to 30% attrition across the semester, we aimed to recruit 139 participants.

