### Compensation

Participants were eligible to receive up to $155 in compensation. Incentives were structured to promote sustained engagement across daily diary completion, device monitoring, and panel assessments. Participants received $1 per completed daily diary (maximum $35), with additional bonuses for achieving ≥ 50% ($15) and ≥ 80% ($15) diary completion. Incentives were also tied to Fitbit data synchronization thresholds based on valid wear days, defined as days with ≥ 1,000 recorded steps. Participants received $10 for syncing valid data on ≥ 50% of study days and another $10 for syncing ≥ 80% of study days. Participants received $10 for each completed monthly panel survey. An early engagement bonus ($10) was awarded to participants who synced valid Fitbit data on ≥ 80% of days (n = 22 days) during the first four weeks of the study. Participants received $10 for completing the second in-person assessment. Participants were permitted to keep the Fitbit device upon study completion.

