As with all longitudinal research in emerging adult populations, several limitations warrant consideration. First, the sample was drawn from a single university and was predominantly White, with relatively few first-generation status college students, which may limit generalizability to more diverse populations of emerging adults transitioning to college. Second, although wearable devices enable continuous free-living monitoring of 24-hour movement behaviors, reliance on proprietary heart rate-informed classification algorithms may introduce measurement imprecision relative to open-source processing of research-grade accelerometry. However, because the present analyses emphasize within-person associations, systematic classification differences are unlikely to meaningfully bias the primary inferences. Third, while mlVAR modeling allows estimation of temporal associations and separation of within- and between-person effects, these analyses do not establish causality; observed lagged relationships should therefore be interpreted as hypothesis-generating. Additionally, although the burst design enhances feasibility and reduces participant burden, intensive symptom assessment occurred during discrete weeks rather than continuously across the semester. As a result, short-lived fluctuations outside burst windows may not have been captured, and temporal inferences rely on pooled observations across individuals. Fourth, daily assessment of suicidality was excluded from the intensive burst protocol due to ethical considerations and the absence of real-time clinical monitoring during unsupervised reporting. Although necessary, this limited examination of the full range of depressive symptoms represented in the PHQ-9 and Diagnostic and Statistical Manual of Mental Disorders, Fifth Edition. Finally, sustained engagement with repeated panel surveys, intensive daily diary bursts, and continuous wearable monitoring across an academic semester may be challenging,^116^ particularly during periods of academic stress or schedule disruption. To mitigate potential attrition and response fatigue, the study incorporated a structured incentive framework, time-limited burst assessments designed to reduce burden, automated reminders within the mobile platform, and routine participant check-ins and personalized prompts delivered by the research team via email.

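### Aim 3 reads differences between calendar-window networks as vulnerability, but its rule cannot separate change within students from change in who, or how many, contribute

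*Protocol article*

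**What the plan says.** In the protocol article, the Aim 3 section states that "time-varying network analyses will be conducted using rolling 7-day calendar windows across the 108-day study period", with an mlVAR model fitted in each window. It justifies pooling as follows: "Although participants contributed data during assigned burst weeks only, pooled daily observations across individuals provide coverage spanning the full academic term". The models are described as "accommodating the unbalanced repeated-measures structure of the burst design". The interpretation rule is: "Periods characterized by increased network connectivity or heightened centrality of specific symptoms or behaviors will be interpreted as potential windows of increased vulnerability". Academic events, including midterms and finals, are then overlaid descriptively.

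Three other sections bear on who contributes to a window:

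- **Sample Size Calculation:** "Allowing for up to 30% attrition across the semester, we aimed to recruit 139 participants".
- **Discussion (limitations):** "sustained engagement with repeated panel surveys, intensive daily diary bursts, and continuous wearable monitoring across an academic semester may be challenging". The article adds that this applies especially in times of academic stress or disrupted schedules. It also concedes that temporal inference depends on pooling across individuals.
- **Study Protocol:** students in sequences S1 or S2 who enrolled after the bursts began have their pre-enrolment burst days coded as missing.

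**The concern.** Reading a stronger network in one window as greater vulnerability assumes that the windows represent comparable students in comparable numbers. The randomised sequences, balanced within each period (Table 1), secure this at assignment. They do not secure it after students stop responding, and the imbalance that Aim 3 says it accommodates is the scheduled one.

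Two features of the plan leave the gap open. First, each window is fitted separately, so a student absent from the last period contributes nothing to its estimates. A single longitudinal model could still have used that student's earlier data. Second, separating within-person from between-person effects does not help, because a window's average edge is still an average over whoever is in it.

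At stake is Aim 3's main product, the statement of when risk intensifies. The periods the article expects to be hardest for engagement are of the same kind as those it plans to overlay on the network estimates.

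**Working it through.** **1. The plan's attrition figure.** 107 × 1.30 = 139.1, which reproduces the target of 139. The 30% is a planning ceiling. It is used below as the upper end, applied to the 144 students enrolled.

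**2. Students per window.** Table 1 places two of the six sequences at each burst position. Assume equal sequence sizes and complete diaries. Seven days give six lag-1 pairs per student.

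| | Students | Lag-1 pairs |
|---|---|---|
| No loss | 144 / 3 = 48 | 48 × 6 = 288 |
| 30% lost by Period 5 | 48 × 0.70 = 33.6 | 33.6 × 6 = 201.6 |

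**3. Effect of number alone (approximation).** For a standardised edge, SE ≈ 1/√pairs, and the mean absolute noise is SE × √(2/π).

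- 288 pairs: SE 0.059, mean absolute noise 0.047.
- 201.6 pairs: SE 0.070, mean absolute noise 0.056.
- Ratio: √(288/201.6) = 1.195, a rise of about 20% in the noise part.

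**4. Simulation with no change in any student's network.** Assumptions: 17 nodes, 7 days per student, pooled lag-1 regression, 300 replicates per scenario. Students have either strong cross-lag edges (0.25) or weak ones (0.05).

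| Students | Share with strong edges | Mean of true edges | Mean absolute edge |
|---|---|---|---|
| 48 | 0.30 | 0.116 | 0.061 |
| 34, non-selective loss | 0.30 | 0.115 | 0.071 |
| 34, selective loss | 0.214 | 0.096 | 0.069 |

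The share 0.214 is 0.30 × 0.50 / 0.70, meaning that half of the strong-edge group leaves.

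- Non-selective loss: the mean absolute edge rises by 0.071/0.061 − 1 = 16%, while the true edges stay put.
- Selective loss: the true edges fall by 1 − 0.096/0.116 = 17%. The mean absolute edge is still above its value at 48 students, because the effect of fewer students outweighs the effect of selection (0.069 against 0.071).

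So the reported metric can rise while the true average edge falls.

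**5. Effect of composition in general.** Apparent shift in the mean edge = share lost × (stayers' mean edge − leavers' mean edge). For an assumed absolute gap of 0.05 to 0.20 and a loss of 10% to 30%, the shift runs from 0.10 × 0.05 = 0.005 to 0.30 × 0.20 = 0.06. Its sign follows the gap, and it is zero if loss is unrelated to the edges.

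**The case against.** The strongest reply has four parts.

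*Selection is assumed.* This stands. The article reports no attrition data, and the edge sizes and withdrawal rates in step 4 are invented. Loss related only to symptom level need not change the edges; it must be related to edge strength. A reader might infer that selective withdrawal will be mistaken for vulnerability. The documents support only that it could be. Nor is the 0.061 to 0.069 rise evidence of selection, since non-selective loss gives a larger one.

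*The article already hedges.* It speaks of potential windows, overlays events descriptively and treats lagged associations as hypothesis-generating. This lowers the severity but gives the analyst no means of separating the two explanations. The article's concession about pooling follows from short-lived fluctuations outside the bursts, not from changing respondents. Its answers to attrition are retention measures.

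*Missing-data methods may sit in an unseen analysis plan.* True, and their absence is not the point. The point is the interpretation rule that the article does state.

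*Different students in different windows are intended.* This also stands. Only loss or late entry on top of the randomised schedule is at issue.

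A reader might also infer from the Compensation section that bonuses run out before Period 5 and so drive late loss. The documents do not support this:

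- Reaching 80% of diaries by the fourth burst needs 28 of 28.
- The 80% Fitbit threshold is 87 days (0.80 × 108 = 86.4). A student onboarded on September 5 (Day 4) reaches it on Day 90 at the earliest, inside Period 5.
- Up to $27 remains payable in Period 5 in any case: $7 for diaries, $10 for the Week 16 panel and $10 for the second visit.

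**Conclusion.** The concern holds in a limited form. As written, the Aim 3 rule cannot distinguish a change within students from a change in who, or how many, contribute to a window.

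The effect of number does not depend on selection. Going from 48 to 34 students raises an unsigned average edge weight by roughly 15–20%. This assumes equal sequences, the full 30% loss, complete diaries among those who remain, and a pooled lag-1 regression in place of mlVAR. It also assumes that edges are averaged without sign and without thresholding, which the article does not specify. A signed average would not be inflated in this way.

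The effect of composition is conditional. Its size and direction cannot be given from the documents. Late entry in S1 and S2 can also thin the earliest windows without any attrition. That finals fall within Days 90–108 is an assumption, as no date is stated.

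This should be changed, because it affects what Aim 3 can conclude about the timing of risk.

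**What to change.** Keep the all-available rolling-window analysis as planned, and add two items to Aim 3.

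1. **A same-student comparison at period level (P1 to P5).** Repeat the comparison in the students who contribute both diary and Fitbit data in the periods being compared. It has to be at period level, because by design only about a third of the cohort is in burst at each position. Each student has one burst per period, so this holds both the composition and the number of students constant. Describe a period as one of heightened vulnerability only with this result reported beside it. Flag any pattern that does not persist as possibly due to a change in respondents.
2. **Contributors per window.** Report the number of contributing students and their baseline PHQ-8 beside each window estimate.

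Inverse-probability weighting for continued response is an optional sensitivity analysis.

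The cost is plan wording and some extra analysis; no new data are needed. At 30% loss, a P1 versus P5 comparison would rest on at most about 144 × 0.70 = 101 students. The same-student estimates are therefore less precise than an all-available analysis at the same level. They also represent more engaged students and cannot locate a change to a particular week, so they serve as a check and do not replace the planned analysis. Completed days per student may still differ between periods, even in the fixed set.
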